## Abstract

**Background:**

While *Chuna* manual therapy is a Korean manual therapy widely used primarily for low back pain (LBP)-related disorders in Korea, well-designed studies on the comparative effectiveness of *Chuna* manual therapy are scarce.

**Methods/design:**

This study is the protocol for a three-armed, multicenter, pragmatic randomized controlled pilot trial. Sixty severe nonacute LBP patients (pain duration of at least 3 weeks, Numeric Rating Scale (NRS) ≥5) will be recruited at four Korean medicine hospitals. Participants will be randomly allocated to the *Chuna* group (*n* = 20), usual care group (*n* = 20), or *Chuna* plus usual care group (*n* = 20) for 6 weeks of treatment. Usual care will consist of orally administered conventional medicine, physical therapy, and back pain care education. The trial will be conducted with outcome assessor and statistician blinding. The primary endpoint will be NRS of LBP at week 7 post randomization. Secondary outcomes include NRS of leg pain, the Oswestry Disability Index (ODI), the Patient Global Impression of Change (PGIC), the Credibility and Expectancy Questionnaire, lumbar range of motion (ROM), the EuroQol-5 Dimension (EQ-5D) health survey, the Health Utility Index III (HUI-III), and economic evaluation and safety data. Post-treatment follow-ups will be conducted at 1, 4, and 10 weeks after conclusion of treatment.

**Discussion:**

This study will assess the comparative effectiveness of *Chuna* manual therapy compared to conventional usual care. Costs and effectiveness (utility) data will be analyzed for exploratory cost-effectiveness analysis. If this pilot study does not reach a definite conclusion due to its small sample size, these results will be used as preliminary results to calculate sample size for future large-scale clinical trials and contribute in the assessment of feasibility of a full-scale multicenter trial.

**Trial registration:**

Clinical Research Information Service (CRIS), KCT0001850. Registered on 17 March 2016.

**Electronic supplementary material:**

The online version of this article (doi:10.1186/s13063-016-1756-8) contains supplementary material, which is available to authorized users.

## Background

### Background and rationale

Low back pain (LBP) is a highly prevalent musculoskeletal disorder that incurs severe pain, increase in sick leave and substantial social costs [1], is disabling to both individual and society and affects approximately 70–80% adults over their lifetimes [2]. Therefore, appropriate LBP treatment selection is of considerable importance for individual patients, physicians, and decision-makers of health care policy.

Spinal manipulative therapy (SMT) is extensively used for acute and chronic LBP, and its efficacy has been reported in numerous randomized controlled trials (RCTs) and systematic reviews (SRs). However, upon closer inspection, the two Cochrane reviews on SMT for acute and chronic LBP mainly use search terms such as manipulation, osteopathy, and chiropractic, and do not include Korean *Chuna* manual therapy or Chinese *Tuina* [3]. Moreover, it can be reasonably inferred that though SMT is widely recommended for both acute and chronic LBP in various guidelines [4–6], the vast disparity in background history, diagnosis and treatment principles and techniques precludes unitary appreciation of treatment effect.

*Chuna*, literally meaning manual treatment in Korean, is a Korean spinal manipulation that has developed absorbing aspects of Chinese *Tuina*, chiropractic manipulation, and osteopathic medicine over time. Manipulative therapy can, therefore, be likened to a reservoir rich with academic contributions from various health care disciplines, drawing from, and emptying into, reserves to form a continuous cycle. *Chuna* incorporates radiology-based diagnosis, which is not customary for Chinese SMT, and includes meridian theory, meridian muscle concepts, and organ pattern identification diagnosis not usually seen in chiropractic manipulation or osteopathic medicine [7]. However, a recent study assessing the *Chuna* literature published from 1995 to May 2013 in Korea reported that clinical studies mainly consisted of case series (*n* = 99; 72%), RCTs (*n* = 15; 11%), and non-RCTs (*n* = 21; 16%) [8]. While the proportion of RCTs in *Chuna*-related studies is steadily increasing, most studies take on an integrative approach as opposed to single treatment, and are not well-equipped to rigorously evaluate its therapeutic effect. Also, in quality assessment of RCTs in accordance with the Consolidated Standards of Reporting Trials (CONSORT) Statement [9], weaknesses regarding identification in title or structured summary in abstract, inadequate trial design description, statistical limitation from small sample size, inaccuracy of randomization and allocation process, difficulty in blinding, and insufficient reporting of participant flow and estimated effect size of interventions and its precision were reported [10].

While *Chuna* manual therapy is primarily used for LBP in Korea with high patient satisfaction [11], it is currently not covered by national health insurance and thus accessibility due to cost is limited considering its high satisfaction rate [12]. The Korean Ministry of Health and Welfare’s 2011 report on usage of Korean medicine shows that *Chuna* was one of the most common usages of Korean medicine [11]. At the 2011 National Assembly forum for insurance guarantee reinforcement of Korean medicine, increasing national insurance coverage of Korean medicine treatments, such as *Chuna* manual therapy, was proposed with the aim of increasing accessibility to Korean medicine services, promoting national health, and improving quality of life [13]. Therefore, well-designed, high-quality RCTs are highly needed in the research sector to determine the effectiveness and economic value of *Chuna* manual therapy and to meet social demand.

### Objectives

Objective evaluation of the comparative effectiveness, safety, and economic evaluation of *Chuna* manual therapy for application in cost-effective, evidence-based practice are important issues both for the Korean medicine sector and for national health services improvement. High-quality RCTs are warranted for rigorous assessment of *Chuna* effectiveness, safety, and cost-effectiveness. The hypotheses of this study are as follows: (1) *Chuna* manual therapy will be more effective and safer than (or equally safe as) conventional usual care in nonacute LBP patients and (2) concurrent treatment consisting of *Chuna* manual therapy and usual care will be more effective than *Chuna* alone or conventional usual care alone in nonacute LBP patients. Therefore, the objectives of this pCRN (pilot *Chuna* Research Network) study are to investigate the following in nonacute LBP patients: (1) the comparative effectiveness and safety of *Chuna* manual therapy compared to conventional usual care through comparison of pain, functionality, quality of life parameters and adverse events, (2) the effectiveness and safety of a concurrent treatment consisting of *Chuna* manual therapy and usual care, which is reflective of actual clinical practice, through comparison of two single treatment groups of *Chuna* manual therapy and usual care, and a combined treatment group of *Chuna* manual therapy with usual care and (3) costs and effectiveness (utility) data of the three groups for exploratory cost-effectiveness analysis (economic evaluation). However, if the current sample size deters this pilot study from reaching a definite conclusion regarding aims (1), (2), and (3), the main objectives of this preliminary study will be to determine a sample size appropriate for statistical testing in future large-scale studies and to assess the feasibility of a full-scale multicenter trial.

## Methods/design

The protocol of this pCRN study is presented in accordance with the 2013 SPIRIT (Standard Protocol Items: Recommendations for Interventional Trials) Statement (see Additional file 1 for the populated SPIRIT Checklist and Table 1 for the trial schedule of enrollment, interventions, and assessments in accordance with recommended SPIRIT figure).

**Table 1 Tab1:** Time points of each assessment index

	Study period										
Time point	Enrollment	Allocation	Active treatment post allocation						Follow-up		
	Week −1	Week 0 (Baseline)	Week 1	Week 2	Week 3	Week 4	Week 5	Week 6	Week 7	Week 10	Week 14
Enrollment											
Eligibility screening	○										
Written informed consent	○										
Vital signs	○								○	○	○
Sociodemographic characteristics, medical history (e.g., LBP, medication history)	○										
Physical examination	○										
Randomized allocation		○									
Interventions											
Treatment in CMT group			←2–3 times/week →				←1–3 times/week →				
Treatment in UC^a^ group (times/week)			←2–3 times/week →				←1–3 times/week →				
Treatment in CMT + UC^a^ group (times/week)			←2–3 times/week →				←1–3 times/week →				
Assessments											
Symptoms and change in medicine		○		○	○	○	○	○	○	○	
NRS of LBP and leg pain	○	○		○	○	○	○	○	○	○	○
ODI		○					○		○	○	
PGIC							○		○	○	
ROM		○					○		○	○	
EQ-5D		○					○		○	○	○
HUI-III		○					○		○	○	○
Economic evaluation		○					○		○	○	○
Adverse events		○	← every visit →						○	○	○

*CMT Chuna* manual therapy, *UC* usual care, *NRS* Numeric Rating Scale, *LBP* low back pain, *ODI* Oswestry Disability Index, *PGIC* Patient Global Impression of Change, *ROM* range of movement, *EQ-5D* EuroQol-5 dimensions, *HUI-III* Health Utility Index III

^a^UC: medication will be administered daily and physical therapy will be applied 2–3 times/week

### Trial design and study setting

This pCRN study employs a multicenter, randomized, three-armed, parallel-group design. Participants will be randomly allocated to the *Chuna* manual therapy group, a usual care group, or a combined treatment group of *Chuna* manual therapy with usual care at a ratio of 1:1:1. Participants will be recruited at four major Korean medicine hospitals in Korea (Pusan National University Korean Medicine Hospital, Kyung Hee University Korean Medicine Hospital at Gangdong, Jaseng Hospital of Korean Medicine, and Mokhuri Neck and Back Hospital) and recruitment period is anticipated to be from February to August 2016. Participants will be recruited through each hospital website and online and offline advertisements. These study sites possess the facilities, personnel, and patient recognition required for LBP patient recruitment, and further information on the study sites is available at Clinical Research Information Service (CRIS registration number: KCT0001850). Participants will receive a total 6 weeks of outpatient treatment for LBP starting from visit 2 through random allocation if deemed eligible in screening at visit 1. General management and treatment processes will adhere to predetermined clinical trial procedures.

The entire research process, design, and setting were prepared through six or more meetings of 22 pCRN members including rehabilitation experts (*n* = 14), clinical research coordinators (*n* = 4), clinical research methodologists (*n* = 2), and economic evaluation experts (*n* = 2) currently employed at six university hospitals, two spine-specialty Korean medicine hospitals, and the Korea Institute of Oriental Medicine (see Additional file 2 for trial committee organization and contributions and role).

### Participants

#### Inclusion criteria

Nonacute LBP participants (with pain duration of 3 weeks or longer) requiring medical attentionParticipants with average Numeric Rating Scale (NRS) ≥5 during the past weekParticipants aged 19 years or older, and 70 years or youngerParticipants who have agreed to trial participation and provided written informed consent

#### Exclusion criteria

Participants diagnosed with serious pathology(s) which may cause LBP (e.g., spinal metastasis of tumor(s), acute fracture, spinal dislocation)Participants with spinal surgery history within the last 3 monthsParticipants with other chronic disease(s) which may interfere with treatment effect or outcome interpretation (e.g., chronic renal failure)Participants with progressive neurologic deficit or severe neurologic symptomsPatients with an inner fixation or stabilization device mounted through spinal surgeryParticipants currently taking steroids, immunosuppressants, medicine for psychological problems or other medication(s) that may interfere with study resultsParticipants who have received *Chuna* manual therapy or medicine which may influence pain levels, such as nonsteroidal anti-inflammatory drugs (NSAIDs), within the past weekPregnant participants or participants who are planning to become pregnantSubjects participating in other clinical studies or who are otherwise deemed unsuitable by the researchers

### Randomization and allocation concealment

A statistician blinded to the objectives and exact design of this study will use SAS 9.3 to generate the allocation sequence using block randomization (block size = 6). Researchers will take care so that block sizes do not become known to the researchers who conduct participant recruitment or intervention allocation.

The researcher conducting participant recruitment at each site (Korean medicine doctor (KMD)) will contact the main trial site for central randomization by phone for random allocation to the three groups at a ratio of 1:1:1 of participants who have voluntarily agreed to participate in the trial, given written informed consent, and been screened and found eligible for trial participation in accordance with inclusion and exclusion criteria. Central randomization by phone will be performed through contact upon participant enrollment by the researcher conducting participant recruitment at each site to a designated independent researcher at the main trial site who will consecutively assign the randomized number and allocation group of each participant by verifying the sequence in the order of phone contact. All allocation numbers will be concealed through blinding of randomized number generation and central phone randomization.

The four sites will receive random allocation competitively on participant enrollment without stratification by site, and each site will respectively stop recruitment when the equal allocated number of 15 participants has been recruited.

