### Blinding

As blinding of physicians and participants to allocation of treatment groups is impossible in the current design due to dissimilarity of interventions, only outcome assessors, statistician and data analysts will be blinded. The outcome assessors will not participate in treatment and a research nurse or KMD blinded to allocation will conduct outcome assessment in a separate room after treatment and will not attempt to become knowledgeable of allocation. The patient will also be cautioned against informing the outcome assessor of treatment allocation prior to each assessment. The electronic data transferred to statistician and data analysts will not contain information on treatment allocation.

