### Adverse events

Physicians will monitor and record any unexpected or unintended patient reaction to *Chuna*, usual care, or its combination at each visit. Adverse events (AEs) associated with *Chuna* will include, but not be limited to, AEs anticipated from previous reports of manual therapy and will stay open to all possibilities taking into consideration other potential, unknown AEs. Physicians will rate the causal relationship between each treatment method and AE occurrence on a 6-point scale (1 = definitely related; 2 = probably related; 3 = possibly related; 4 = probably not related; 5 = definitely not related; and 6 = unknown), and all AEs will be categorized into three levels using the Spilker classification (mild (1) = not needing additional intervention, nor significantly inhibiting to the normal lifestyle (function) of the participant; moderate (2) = significantly inhibiting to the normal lifestyle (function) of the participant, and may need additional intervention, recovering afterwards; and severe (3) = severe AE requiring intensive intervention, and leaving sequelae). In the case of “serious adverse event (SAE)” during study duration, unblinding is permissible and the relevant Institutional Review Board (IRB) and main study site (Pusan National University Korean Medicine Hospital) will be informed and will decide whether the trial will continue or be terminated. In the event that a subject suffers direct injury associated with the clinical trial, the subject may receive appropriate medical action as seen fit by the subinvestigator, and damage compensation will follow prespecified clinical research insurance clauses. All study participants will be provided with an emergency contact number to the principal investigator or subinvestigator for any questions, medical issues or research-related diseases during the study and accordingly receive requested services.

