### Data monitoring and safety monitoring

This study is a pilot study with no interim analysis, and a data monitoring committee was not organized as no SAEs regarding *Chuna* or usual care not previously reported are expected to occur.

Safety assessment will mainly assess frequency of AEs, including all SAEs. AE reports will summarize the number and percentage of participants who experienced AEs, and will include categorized information on body region of AE manifestation. Other data (e.g., severity, causal relationship with treatment) will be included in safety monitoring reports.

An outside CRO will be entrusted with safety and data monitoring. CRO monitoring will consist of three sessions in the following order: initiative monitoring at first subject enrollment, one midterm monitoring during the clinical trial, and conclusive monitoring upon completion of clinical trial. Participant safety data and CRF and source documents will be reviewed and crosschecked to confirm participant safety and data integrity.

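### The single block size of 6 is printed beside a safeguard that needs it hidden; the resulting exposure is small and confined to the main site and to a lagging last site

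*Protocol article*

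**What the plan says.** All references are to the protocol article.

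- **Randomization and allocation concealment.** The statistician will "generate the allocation sequence using block randomization (block size = 6"), for "random allocation to the three groups at a ratio of 1:1:1". One size is given, so each block holds two patients per arm. The next sentence reads: "Researchers will take care so that block sizes do not become known to the researchers who conduct participant recruitment or intervention allocation".
- **Same section.** The recruiting doctor telephones after consent and confirmed eligibility. The call goes to "a designated independent researcher at the main trial site who will consecutively assign the randomized number and allocation group of each participant". There is one list for all four hospitals, used in order of calls and not stratified by site, and "each site will respectively stop recruitment when the equal allocated number of 15 participants has been recruited".
- **Blinding.** Blinding of physicians and participants is called impossible, and "only outcome assessors, statistician and data analysts will be blinded".
- **Adverse events** names the "main study site (Pusan National University Korean Medicine Hospital"). **Trial design and study setting** lists the same hospital among the four that recruit.

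**The concern.** Concealment under a fixed block rests on two things: the recruiter must not know the block size, and must not see the earlier assignments in the current block. Here the size is a constant printed next to the promise to hide it. Because treatment is open, each site sees its own past assignments as they accrue.

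Two further rules matter. The list is read out inside a hospital that also recruits. The cap of 15 per site means that the slowest site fills the last places alone and sees every assignment there, with a known end point at patient 60.

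A recruiter who can narrow down the next arm can delay or decline a particular patient before making the call. The exclusion criteria include a discretionary judgement of unsuitability, the primary outcome is a self-reported pain score, and the main group comparisons (t test, ANOVA) are unadjusted. With 20 patients per arm, a few steered enrolments could matter.

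**Working it through.** **Inputs from the article:** three arms at 1:1:1; block of 6; four sites with a cap of 15; 60 patients. These agree: 4 × 15 = 60 = 10 × 6, so the list ends on a block boundary. **Assumed:** site recruitment rates, which the article does not give.

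**1. Someone who sees every earlier assignment and knows the block size.** There are 6!/(2!·2!·2!) = 90 equally likely blocks.

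| Place in block | 1 | 2 | 3 | 4 | 5 | 6 | Mean |
|---|---|---|---|---|---|---|---|
| Next arm certain | 0 | 0 | 0 | 0 | 0.20 | 1 | 0.200 |
| At least one arm ruled out | 0 | 0 | 0.20 | 0.60 | 1 | 1 | 0.467 |
| Best guess correct | 0.333 | 0.400 | 0.500 | 0.533 | 0.600 | 1 | 0.561 |

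For example, place 5 is certain when the last two places belong to the same arm: 3/15 = 0.20. At place 4, an arm is ruled out unless the first three places are all different: 1 − 8/20 = 0.60. Chance is 0.333.

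One site can act only on its own 15 patients: 0.200 × 15 = 3 certain, and 0.467 × 15 = 7 with an arm ruled out.

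**2. A recruiter who sees only their own site.** This was simulated with four sites sharing the list, each closing at 15, and the recruiter generously assumed to know where each block starts. At equal rates about 0.4% of assignments are certain (0.004 × 15 ≈ 0.06 patients), at least one arm is ruled out for 5.7%, and 38% to 39% of guesses are correct. For a site recruiting three times as fast as the others, the certain share is 1.0% and correct guesses are 42%.

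**3. The last site alone at the end of the list.**

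| Assumed rates | Mean patients in solo tail | Chance of 6 or more | Best guess correct in tail |
|---|---|---|---|
| Equal | 3.2 | 14% | 45% to 49% |
| One site at half speed | about 6.1 | 58% | 51% to 52% |

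The ranges in the last column are the spread between separate simulation runs. In extra correct guesses over the whole trial:
- equal rates: 3.2 × (0.45 − 0.333) ≈ 0.4, up to 3.2 × (0.49 − 0.333) ≈ 0.5;
- half speed: 6.1 × (0.52 − 0.333) ≈ 1.1.

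More extreme lags raise the certain share of that site's 15 patients to 11% at a quarter of the others' speed, and to 16% if it fills the last 15 places alone. That is 1.6 and 2.4 patients.

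**4. Block sizes 6, 9 and 12 in random order.** The observer sees the whole sequence and knows the set of sizes but not their order.

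| | Fixed 6 | Random 6/9/12 |
|---|---|---|
| Certain | 20% | about 2% |
| At least one arm ruled out | 47% | about 7% |
| Best guess correct | 56% | 52% |

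The change removes near-certainty. It hardly changes average guessing.

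**The case against.** The case on the other side is strong, and most of it stands.

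- **A reader might infer that site recruiters in general can work out the next arm.** The article does not support this. The list is central and unstratified, and the call follows consent and eligibility, so nobody can be excluded once the arm is disclosed. Step 2 shows almost nothing to deduce from one site's view. An earlier decision to delay or decline would still be possible.
- **A reader might also take 20% and 47% of all 60 patients, that is 12 and 28, as exposed.** That would need one person who sees all four sites and controls every enrolment. No such person is described.
- **A reader might conclude that concealment was broken.** The article calls the list holder independent and shows no leak. It does not show that recruiters had the printed block size. Details of the holder's separation may stand in the full protocol or operating procedures.
- **Varying the block size does nothing about a list holder**, who knows the next arm whatever the block size. This is correct, and that person's separation has to be dealt with on its own.
- **Baseline-adjusted ANCOVA is planned.** It is a secondary analysis, so only a partial check.

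What remains is that the stated safeguard depends on hiding a constant that the same paragraph discloses, and that the list sits in a recruiting hospital without a stated rule of separation.

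**Conclusion.** The point holds as an avoidable weakness in concealment, limited in size. For an ordinary site recruiter it is negligible. It reaches about 3 certain assignments and 7 with an arm ruled out among the main site's 15 patients, but only if someone there learns the running sequence across sites. In the tail it averages about 3 patients at equal rates and about 6 if one site recruits at half speed, worth roughly half an extra correct guess and one extra correct guess respectively.

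The tail figures rest on assumed recruitment rates, and on a recruiter who knows the block size and the position in the list. No bias in the pain score is shown or estimated. The change is worth making because it is cheap, and because the same network plans a full-scale trial that may reuse the procedure.

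**What to change.** In Randomization and allocation concealment:

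1. Replace the single block size with randomly varying sizes, for example 6, 9 and 12, generated by the same statistician in the same SAS program. Keep the sizes out of the protocol and site documents. The cost is a few program lines and a change of wording. The downside is that arm sizes may differ by a few patients if enrolment ends inside a block; a block of 12 holds 4 per arm, so two arms could differ by at most 4.
2. State that the list holder takes no part in recruitment or treatment at the main site and does not share past assignments. This costs one sentence if it is already the practice.

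Moving the telephone list to the contract research organization is optional. The article says "An outside CRO will be entrusted with safety and data monitoring", but it describes three monitoring sessions, and Data collection and management ties the organization to the lead site. Neither its capacity for a running telephone service nor its separation from that site is shown, so this step cannot be assumed to be cheap.
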